## Abstract

The subcutaneous implantable cardioverter-defibrillator (S-ICD) was developed to reduce complications associated with transvenous leads while preserving efficacy in terminating malignant ventricular arrhythmias. However, current evidence supporting the S-ICD is primarily derived from industry-sponsored studies and highly specialized centers. This study aims to offer a comprehensive, nationwide, real-world assessment of all patients who underwent S-ICD implantation in France. The HONEST (coHOrte fraNcaise des dEfibrillateurs Sous cuTanés) cohort is a French nationwide, single-arm, observational ongoing study that enrolled all patients who underwent implantation of an S-ICD (EMBLEM, Boston Scientific) between October 2012 (the first implantation in France) and December 2019. Clinical endpoints are centrally adjudicated. Overall, 4,924 (77% males; 49.9 years) patients, representing 98.2% of all S-ICD implantations during the study period in France, were included. The HONEST study represents the first nationwide cohort evaluating S-ICD recipients to provide contemporary, real-world data. Its goal is to identify areas for improvement and refine strategies to prevent sudden cardiac death. (S-ICD French Cohort Study [HONEST]; NCT05302115)

## Background and rationale

The need to improve current strategies for the prevention of sudden cardiac death (SCD), potentially through emerging technologies, is well recognized.^1^, ^2^, ^3^, ^4^, ^5^ While transvenous implantable cardioverter-defibrillators (ICDs) have proven effective in preventing SCD in high-risk patients,^6^^,^^7^ complications related to transvenous leads, such as infection and lead dysfunction, have prompted the development of the entirely subcutaneous ICD (S-ICD).^8^

Multiple studies have demonstrated the efficacy of the S-ICD in terminating life-threatening ventricular arrhythmias, while highlighting its lower risk of systemic infection and lead-related complications, compared with traditional transvenous ICDs.^9^^,^^10^ However, the S-ICD also presents limitations, most notably, the inability to provide bradycardia pacing or antitachycardia pacing, which may be a significant drawback for certain patients. Additionally, as with any novel device, concerns about hardware malfunctions and product recalls persist, potentially resulting in serious clinical consequences. These limitations underscore the importance of independent, rigorous postmarket surveillance to ensure long-term safety and efficacy.^11^^,^^12^ To date, much of the evidence supporting the S-ICD has been derived from industry-sponsored studies conducted in highly specialized centers, often involving modest sample sizes. This may introduce bias and limit the generalizability of findings to broader, real-world populations (Figure 1).^13^, ^14^, ^15^, ^16^, ^17^

**Figure 1 fig1:**
[figure not shown]
**Major Studies Assessing S-ICD Since 2013** Observational studies have a yellow background, and randomized control trials have a blue background. IDE = Investigational Device Exemption; PAS = Post Approval Study; S-ICD = subcutaneous implantable cardioverter-defibrillator.

The HONEST (coHOrte fraNcaise des dEfibrillateurs Sous cuTanés) cohort was designed to generate objective, unbiased, real-world data on a large population of S-ICD recipients, supported by rigorous, independent adjudication of clinical events. Initiated in 2018, the study benefits from the fact that the S-ICD is produced by a single manufacturer, allowing comprehensive, nationwide data collection. In addition, remote monitoring enables close follow-up of device function and clinical outcomes, ensuring consistent data quality throughout the study.

## Methods

### Design

The HONEST cohort is a French nationwide, single-arm, observational ongoing study that enrolled all patients who underwent implantation of an S-ICD (EMBLEM, Boston Scientific) between October 2012 (date of the first implantation in France) and December 2019 (Central Illustration). The study includes all 150 French Hospitals accredited to perform S-ICD implantations (Supplemental Table 1).

**Central Illustration fig4:**
[figure not shown]
**The HONEST Study is a Nationwide Cohort of 4,924 S-ICD Recipients, Representing 98.2% of All Patients Implanted With an S-ICD in France Between October 2012 and December 2019** The cohort will provide comprehensive long-term evidence on outcomes associated with S-ICD therapy, thereby informing its safety, effectiveness, and real-world clinical utility. Beyond describing outcomes, HONEST also constitutes a robust research platform to support focused analyses and to refine contemporary approaches to sudden cardiac death prevention. HONEST = coHOrte fraNcaise des dEfibrillateurs Sous cuTanés; other abbreviation as in Figure 1.

Initiated in 2018 in collaboration with the French Society of Cardiology and part of the DAI-PP (Défibrillateur Automatique Implantable-Prévention Primaire) Research Network research program, the study was approved by Commission Nationale de l'Informatique et des Libertés, the French Data Protection Authority, under registration number CNIL2217196. It adheres to the principles of the Declaration of Helsinki and is registered at ClinicalTrials.gov (NCT05302115).

### Inclusion criteria

Patients were eligible for inclusion in the HONEST cohort if they met the following criteria:1.Underwent implantation of an S-ICD (EMBLEM, Boston Scientific) in France between October 2012 and December 2019;2.Provided informed consent to participate in the HONEST study, in accordance with the French MR-004 reference methodology for observational research involving human subjects.

### Exclusion criteria

The only exclusion criterion was refusal to provide informed consent in accordance with the MR-004 reference methodology.

### Study protocol

#### Inclusion and clinical follow-up

All patients who underwent S-ICD implantation in France since the first procedure in October 2012 were invited to participate in the HONEST study and to be continuously monitored via the Latitude remote monitoring system (Boston Scientific).

Boston Scientific, the sole manufacturer of the S-ICD, provided a comprehensive list of serial numbers corresponding to all S-ICD devices distributed in France from October 1, 2012, to December 31, 2019, categorized by implanting center. These serial numbers were shared with all 150 accredited S-ICD implantation centers to allow patient identification and inclusion. During the study period (October 1, 2012 to December 31, 2019), a total of 5,175 S-ICD devices were distributed in France. Of these, 31 generators had been distributed to participating centers by the manufacturer but had not yet been implanted as of December 31, 2019, leaving 5,144 implanted S-ICDs. Among implanted devices, 91 patients declined participation. The HONEST cohort therefore includes 5,053 implanted S-ICD procedures, comprising 4,924 de novo implantations and 129 generator replacements. Overall, this corresponds to the capture of 98.2% of all S-ICD implantations performed in France during the study period (Figure 2). Participating centers included 39 university hospitals, 60 nonuniversity teaching hospitals, and 51 private institutions.

**Figure 2 fig2:**
[figure not shown]
**Study Flowchart** The serial numbers corresponding to all S-ICD devices distributed in France from October 1, 2012, to December 31, 2019, were collected. Among 5,175 devices identified, 31 generators had been distributed to participating centers by the manufacturer but had not yet been implanted as of December 31, 2019, and 91 patients declined to participate. The final study population included 4,924 patients with de novo S-ICD implantation and 129 generator replacements, representing 98.2% of all patients implanted with an S-ICD in France during the study period. Abbreviation as in Figure 1.

Patient data, including baseline characteristics, procedural details, and follow-up events, were retrospectively collected in 2019/2020.^18^ A prospective follow-up phase began in 2020 and is planned to continue annually for 10 years.

A prespecified electronic case report form was used to collect the following data: demographic variables, indication for ICD therapy (primary vs secondary prevention), underlying heart disease (diagnosis and specific characteristics), left ventricular ejection fraction, procedural data (including anesthesia modalities, S-ICD generator model [EMBLEM model 1010, A209 or A219], use of defibrillation testing, need of an additional pacing system, among others), and follow-up data, including the use of remote monitoring (Latitude, Boston Scientific) and the occurrence and exact timing of clinical events. These events included device-related complications, appropriate or inappropriate therapies, reinterventions, heart transplantation, and death. Moreover, patients’ genetic findings, along with raw intracardiac electrograms data recorded during electric shocks, are systematically collected. A complete list of collected outcome events is provided in Supplemental Table 2.

#### Study endpoints

The primary study outcomes at 5 and 10 years include 1) the cumulative incidence of appropriate shocks; 2) device-related complications, including inappropriate therapies, infection, lead dysfunction, and manufacturer-related recalls; 3) all-cause and cause-specific mortalities; and 4) requirement for pacing during follow-up.

An appropriate S-ICD shock was defined as any shock delivered for a ventricular arrhythmia with a ventricular rate exceeding the programmed therapy zone. Inappropriate shocks were defined as those triggered by nonventricular arrhythmias, T-wave oversensing, myocardial signals, or electromagnetic interference. Notably, shocks resulting from double counting of T-wave oversensing during slow ventricular tachycardia below the programmed therapy threshold was defined as inappropriate shock therapy. Surgical reintervention was defined as any procedure performed after initial implantation due to device-related complications. Local complications included premature battery depletion or pocket-related issues such as hematoma, localized or systemic infection, poor wound healing, and lead dislodgment. Early complications were defined as adverse events occurring within the first 30 days following S-ICD implantation. Late complications were defined as adverse events occurring beyond 30 days after S-ICD implantation.

### Data management and study organization

Study data were centrally collected and managed using REDCap electronic data capture tools hosted at the Paris Cardiovascular Research Center (U 970, European Georges Pompidou Hospital, Paris, France). Specific REDCap modules were created for each work package to streamline data entry and review.

A steering and scientific committee oversaw study conduct, data quality, and progress (Supplemental Table 3). Participating sites entered S-ICD shocks and device- or procedure-related complications into a centralized database. In parallel, an independent external research assistant reviewed source documentation from electronic health records and S-ICD interrogations, including stored electrograms, to verify, harmonize, and standardize site-reported data across centers. A dedicated adjudication committee conducted centralized reviews of key clinical endpoints, including cause of death (with specific focus on SCD and S-ICD–related deaths), device infections, lead-related complications, and shock episodes. Electrograms were systematically retrieved via remote monitoring. Among all recorded shocks, electrograms were independently reviewed in a blinded manner by 2 expert electrophysiologists in 81% to classify shocks as appropriate or inappropriate and determine the underlying rhythm mechanism. Any discordance between adjudicators or between central adjudication and site assessment was resolved by discussion and final determination during annual consensus meetings. To minimize loss to follow-up, a systematic process was implemented across all 150 participating centers to ensure completeness of longitudinal data. Notably, the study collects all events, not just the first occurrence, for outcomes such as appropriate therapies, enabling a comprehensive assessment of event burden over time.^19^ Finally, vital status is comprehensively ascertained through systematic cross-referencing with the National Institute of Statistics and Economic Studies (INSEE, France) database.

The HONEST study was initiated and is coordinated by the French Institute of Health and Medical Research (INSERM Unit 970) and the French Society of Cardiology. This investigator-initiated study is fully independent and received no industry funding. Of note, Boston Scientific had no involvement in the study design, data collection, analysis, interpretation, or the preparation of this report. The authors retain full responsibility for the study design, data analysis, manuscript preparation, and its final content.

### Statistical considerations

Categorical data are summarized as numbers and percentages, while continuous data are presented as mean values with SDs or as median values with IQRs, as appropriate. Cumulative incidence curves will be generated with the use of the Aalen–Johansen estimator, which accounts for competing events (eg, cardiovascular and noncardiovascular death). For noncompeting events, Kaplan-Meier curves will be used. Since the risk of events is not constant over time, cumulative incidence will be presented instead of incidence rates. For repeated events (eg, appropriate and inappropriate shocks and complications), cumulative hazard rate will be provided using the Nelson-Aalen estimator.

For multivariate analysis, a Cox proportional hazards model will be employed, using the Breslow method to handle tied event times. Time until events is recorded in days to minimize ties. A frailty term will be included to account for variability between trial sites, with center effects embedded as random to capture differences in clinical practices and center experience. For competing events (eg cause-specific deaths), both cause-specific hazard rate and subdistribution hazard rates will be calculated, with the Fine and Gray model used for sensitivity analyses. Prespecified predictors will be 1) patient characteristics (eg, age, sex, body mass index, prevention type [primary vs secondary], underlying heart disease category, left ventricular ejection fraction, prior ICD); 2) procedural/device characteristics (eg, incision technique [2-incision vs 3-incision], generator position [intermuscular vs subcutaneous], anesthesia type, defibrillation testing [performed vs not], device generation/type, SmartPass filter status); and 3) calendar time/center factors (eg, implant year/era, implanting center volume), when available.

For the analysis of appropriate and inappropriate shocks, the Anderson and Gill model will be applied, incorporating a robust sandwich variance estimator to correct for correlations between recurrent events within the same subject. Shocks occurring within the same episode (cluster) will be counted as a single shock. As a sensitivity analysis, a negative binomial model will be used to account for all shock episodes. For complications and complications requiring intervention, the Wei, Lin and Weissfeld model will be employed to account for repeated events of different nature, identifying factors associated with increased or reduced risks. The center effect will be examined as a fixed effect, categorized by centers with S-ICD implantation volumes greater or <100.

Follow-up will be censored in cases of loss to follow-up, device removal, death, or at the study’s end. The proportional hazards assumption will be assessed using statistical tests and graphical diagnostics based on scaled Schoenfeld residuals. Missing data will be described and handled using multiple imputation strategies. Clinically relevant variables and variables known to be outcome-related from existing literature will be included in the models.

Adjusted subgroup comparisons will be performed using inverse probability weighting based on propensity scores derived from logistic regression models incorporating age, body mass index, indication (primary vs secondary prevention), underlying heart disease, left ventricular ejection fraction, concomitant pacing system, prior ICD, anesthesia type, number of incisions, generator position, generator generation/type, and use of the SmartPass filter. Covariate balance before and after weighting will be evaluated using standardized mean differences, with standardized mean differences <0.10 indicating adequate balance, and will be visualized using Love plots.

To account for potential temporal confounding, outcomes will be analyzed stratified by calendar period and/or device generation, enabling interpretation of event rates in the context of evolving technology and clinical practice.

To quantify the precision afforded by the cohort size, we prespecified expected 95% CI widths for adverse event proportions in the full cohort and calculated illustrative minimum detectable effect sizes for two-group comparisons at 80% and 90% power (two-sided α = 0.05). For time-to-event endpoints, detectable HRs were estimated as a function of the expected number of observed events using the Schoenfeld approximation. These calculations are summarized in Supplemental Tables 4 to 6.

A 2-sided *P* value <0.05 will be considered statistically significant without alpha correction. All data are analyzed at French Institute of Health and Medical Research, Unit 970, Paris Cardiovascular Research Center, Paris, using the *R* software (R Project for Statistical Computing).

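### With death censored, the Nelson-Aalen curve for repeated shocks and complications is a rate while alive with the device, not the event burden per implanted patient

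*Protocol article*

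**What the plan says.** All statements are in the Methods of the protocol article.

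- **Repeated events.** Under Statistical considerations: "For repeated events (eg, appropriate and inappropriate shocks and complications"), the article says that a "cumulative hazard rate will be provided using the Nelson-Aalen estimator".
- **Censoring.** The same section says: "Follow-up will be censored in cases of loss to follow-up, device removal, death, or at the study’s end". No analysis is exempted.
- **Cumulative incidence.** The same section uses the "Aalen–Johansen estimator, which accounts for competing events (eg, cardiovascular and noncardiovascular death").
- **Purpose of the repeated-event data.** Under Data management and study organization, all events and not only the first are collected, "enabling a comprehensive assessment of event burden over time".
- **Regression for shocks.** An Andersen-Gill model is planned, "incorporating a robust sandwich variance estimator to correct for correlations between recurrent events within the same subject". In addition, "Shocks occurring within the same episode (cluster) will be counted as a single shock". No variance or confidence-interval method is stated for the Nelson-Aalen curve.

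**The concern.** Death ends the possibility of further shocks or complications. If it is handled as censoring, the Nelson-Aalen estimator adds up the event rate among those still at risk, as though that rate went on applying to everyone implanted. The sum answers how fast events accrue in a patient who stays alive with the device. Burden in an implanted cohort is more naturally the average number of events that a recipient actually experiences, and patients who die early contribute few.

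The article recognises this for cumulative incidence and then names an estimator for repeated events in which death plays no part. The same death would thus be treated in two ways in shock curves that are likely to be read side by side. At stake is the burden figure at the long horizons. Mortality is itself among the primary outcomes at 5 and 10 years, and follow-up of up to 10 years is presented in the Discussion as a strength of the study. The gap between the two quantities grows with both time and mortality.

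**Working it through.** The article gives no mortality rate, no shock rate and no figure for this curve, so there is nothing to reproduce. Supplemental Tables 4 to 6 are not shown. The sizes below rest on stated assumptions.

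**Inputs.** Horizons of T = 5 and 10 years (Study endpoints) and a cohort of 4,924 patients (Preliminary results). Assumed: death hazard m of 0.02, 0.03 or 0.05 per year, and a constant event rate r while alive.

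**Formulas.**
- Nelson-Aalen with death censored estimates R(T) = rT.
- The mean number of events per patient is the integral of S(t-)dR(t), here r(1 - exp(-mT))/m.
- The ratio of the two is mT/(1 - exp(-mT)); r cancels.

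| m per year | T = 5 | T = 10 |
|---|---|---|
| 0.02 | 0.10/0.0952 = 1.05 | 0.20/0.1813 = 1.10 |
| 0.03 | 0.15/0.1393 = 1.08 | 0.30/0.2592 = 1.16 |
| 0.05 | 0.25/0.2212 = 1.13 | 0.50/0.3935 = 1.27 |

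The same formula over an assumed 10-year survival of 90% to 60% gives 1.03 to 1.13 at 5 years and 1.05 to 1.28 at 10 years.

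**In events.** With an assumed r = 0.03 episodes per patient-year and m = 0.03, the 10-year curve reads 0.300 and the mean per patient is 0.259. Multiplied by 4,924, that is about 1,477 against 1,276 episodes.

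**Simulation check.** With 4,924 patients, 10 years and 200 runs per setting, Nelson-Aalen divided by the Ghosh-Lin estimate at 10 years was about 1.12 for 80% survival and 1.19 for 70%, as the formula predicts. In one large run in which event-prone patients also died sooner, the actual mean was 0.415 events per patient by 10 years. Ghosh-Lin gave 0.415 and Nelson-Aalen 0.455, a ratio of 1.10.

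**Events that come early.** The article itself says that event risk varies over time. Suppose that the event rate halves every 2 years (k = ln 2/2 = 0.347) and m = 0.03. The ratio is then [(1 - exp(-kT))/k] / [(1 - exp(-(k+m)T))/(k+m)]:
- T = 5: 2.375/2.251 = 1.055, against 1.08 with a constant rate.
- T = 10: 2.795/2.594 = 1.08, against 1.16 with a constant rate.

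**The case against.** The strongest reply is that the article promises a cumulative hazard rate and never calls it events per patient. Nelson-Aalen with death censored estimates the cumulative rate among patients alive and under follow-up, which is close to that label. The remark about burden explains why all events are collected and names no estimator. This stands: the estimator is not invalid, and the overstatement exists only when the curve is read as burden per patient. What remains is that the article invites that reading and names nothing else that would supply the number.

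It also stands that the first primary outcome, the cumulative incidence of appropriate shocks, is unaffected, because cumulative incidence accounts for death. The mortality and event rates used above are assumptions.

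A reader might infer two stronger criticisms that the document does not support.

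1. *Nelson-Aalen subgroup curves mix shock rate with mortality.* In the simple model it is the other way round: the Nelson-Aalen curve is rT, free of m, while the survival-weighted mean depends on m. Two subgroups with equal event rates and unequal mortality would share a Nelson-Aalen curve and differ in burden. If death is related to event-proneness, the Nelson-Aalen curve reflects selected survivors, but it is still the rate among those alive.
2. *The confidence bands will be too narrow.* The usual Poisson-type variance would be too small if episodes cluster within patients. In the simulation, frailty variances of 2 to 10 with 0.03 to 0.06 episodes per patient-year made its standard error about 20 to 60% too small. But the article does not commit to that variance for the curve, it collapses shocks within an episode, it uses a robust variance for Andersen-Gill, and it plans a negative binomial sensitivity analysis. A condensed article may leave the interval method for a descriptive curve to the full plan.

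**Conclusion.** The point holds as a mismatch between the estimator and one stated use of the data. The planned curve is a valid cumulative rate while alive with the device, and the plan lacks an estimate of the mean number of events per implanted patient. Used as that mean, the curve would be too high by about 5 to 13% at 5 years and 10 to 27% at 10 years. This rests on assumed mortality of 2 to 5% per year, a constant event rate and death unrelated to event rate. With an event rate that halves every 2 years and 3% mortality, the excess falls to about 5 to 6% at 5 years and 8% at 10 years. It should be corrected because it is material at 10 years and cheap to put right. It does not threaten the design or the cumulative incidence outcomes.

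**What to change.** - Report the mean cumulative number of shocks and of complications per implanted patient, with death as a terminal event (Ghosh-Lin or Cook-Lawless estimator), as the burden estimate.
- Give it patient-level robust or bootstrap confidence bands, in line with the robust variance already planned for the Andersen-Gill model.
- Keep the Nelson-Aalen curve beside it, labelled as the cumulative rate while alive with the device, for comparing event rates between subgroups.
- State in one sentence whether device removal stays a censoring event in the burden estimate, since the article lists it with death.

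No new data are needed: event times are recorded, vital status is ascertained by linkage to the national statistics institute, and the analysis is already in R. The cost is one extra estimator, one extra curve to explain and a somewhat lower burden figure.

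### Technique hazard ratios from the frailty Cox model can remain partly confounded by centre, because the plan relies on a random centre effect and states no within-centre contrast to set beside it

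*Protocol article*

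**What the plan says.** All of this is in the protocol article, under Statistical considerations unless noted.

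- Centre enters the Cox model as a random effect: "A frailty term will be included to account for variability between trial sites". Its stated purpose is given in the same sentence: "with center effects embedded as random to capture differences in clinical practices and center experience".
- The prespecified predictors include practices: "incision technique [2-incision vs 3-incision], generator position [intermuscular vs subcutaneous], anesthesia type, defibrillation testing [performed vs not". They also include patient characteristics (age, sex, body mass index, prevention type, heart disease category, ejection fraction, prior ICD) and "calendar time/center factors (eg, implant year/era, implanting center volume), when available".
- After the models for shocks and complications, a second treatment of centre appears: "The center effect will be examined as a fixed effect, categorized by centers with S-ICD implantation volumes greater or <100". This is a two-class volume variable, not one effect per centre.
- Adjusted subgroup comparisons use "inverse probability weighting based on propensity scores derived from logistic regression models incorporating age, body mass index, indication" and further patient and procedural items. Neither centre nor centre volume is on that list.
- Outcomes are also to be stratified by calendar period and/or device generation.
- On scale, the Design section says: "The study includes all 150 French Hospitals accredited to perform S-ICD implantations". The cohort has 4,924 de novo implantations.

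The article nowhere states a baseline hazard stratified by centre, centre-specific fixed effects, or a split of a practice effect into within-centre and between-centre parts.

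**The concern.** A shared frailty model treats the centre effect as a draw that is unrelated to the covariates. Here the reason given for the frailty is that centres differ in practice and experience, and several of those practices are the exposures of interest. Centres that adopt a technique may also differ in referral, operator skill or unmeasured case mix. If so, the technique coefficient blends two contrasts: patients treated differently within a centre, and centres that work differently. The frailty absorbs only part of the second when events per centre are few, because centre effects are then shrunk towards zero.

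The Discussion names defibrillation testing and anesthesia modality as questions for the cohort to answer, and significance is declared at two-sided P < 0.05 without correction. A technique favoured by higher-risk centres could look harmful, and one favoured by lower-risk centres protective. Nothing in the stated analysis would show that the signal came from the centres.

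**Working it through.** The article gives no centre variance, no distribution of technique by centre and no technique hazard ratio, so there is no stated figure to reproduce. The check is therefore one of mechanism and plausible size.

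**Step 1: information per centre.** 4,924 / 150 = 32.8 patients per centre on average. At an assumed event risk of 8%, that is 32.8 x 0.08 = 2.6 events.

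**Step 2: shrinkage.** In a gamma frailty model with variance θ, the weight given to a centre's own observed/expected ratio is E / (E + 1/θ), where E is its expected number of events. I take θ as roughly the square of the centre log-hazard SD.

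- SD 0.4 (θ = 0.16): 2.6 / (2.6 + 6.25) = 0.29.
- SD 0.3 (θ = 0.09): 2.6 / (2.6 + 11.1) = 0.19.
- A centre with 100 patients (E = 8): 8 / 14.25 = 0.56 and 8 / 19.1 = 0.42.

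Shrinkage is strong in an average centre and milder in a large one.

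**Step 3: simulation over a grid.** 150 centres of skewed size, about 4,924 patients, 5 years of follow-up, constant hazard, true technique HR 1.00, 120 runs per scenario. Assumed inputs: 5-year risk 5% or 15%; centre log-hazard SD 0.3 or 0.5; SD of the centre's logit probability of using the technique 1 or 2; correlation between the two 0, 0.3 or 0.6. Range of mean HR across scenarios:

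| Correlation | Crude | Frailty | Frailty + centre proportion | Within centre (stratified) |
|---|---|---|---|---|
| 0 | 0.99-1.01 | 0.99-1.02 | 0.98-1.02 | 0.98-1.02 |
| 0.3 | 1.07-1.21 | 1.05-1.14 | 0.98-1.02 | 0.98-1.01 |
| 0.6 | 1.16-1.43 | 1.10-1.29 | 0.99-1.05 | 0.99-1.01 |

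The share of crude log-HR bias removed by the frailty is 1 - ln(HR frailty) / ln(HR crude). It runs from 1 - ln 1.212 / ln 1.244 = 12% to 1 - ln 1.108 / ln 1.284 = 59%.

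**Step 4: the narrower range.** Further runs, with all inputs again assumed:

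- Skewed centre sizes and about 8.5% risk: frailty HR 1.00 at correlation 0, 1.08 at 0.3 and 1.15 at 0.5, against 0.99-1.00 with the centre proportion added.
- SD 0.35, correlation 0.3, about 400 events: 1.05-1.08.
- SD 0.3-0.4, correlation 0.3-0.5, about 415 events: 1.12-1.23. This set lies above the two just listed, so I treat it as the upper edge.

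Together these support about 1.05-1.2. With the opposite sign of correlation, relabelling the technique gives the reciprocals: 1/1.2 = 0.83 to 1/1.05 = 0.95.

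**Step 5: does the planned volume term close the gap?** Setting: 8% risk, centre risk correlated 0.3 with log volume.

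| Added to the frailty model | SD 0.4, correlation 0.5 | SD 0.3, correlation 0.3 |
|---|---|---|
| Log volume | 1.16 | 1.06 |
| Volume cut at 100 | 1.17 | 1.07 |
| Centre proportion using the technique | 1.01 | 0.99 |

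Volume removes only the part of centre risk that travels with volume.

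**Step 6: price in precision.** In the grid, the SD of the within-centre log HR against the frailty one was 0.080 / 0.078 = 1.03 with moderate clustering of technique and 0.183 / 0.143 = 1.28 with strong clustering. In another set the standard error rose from 0.107 to 0.128-0.149 (ratios 1.20 and 1.39), and in a third by 10-15%.

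**The case against.** The strongest reply is that this is a standard model used in a standard way. With measured practices as covariates, the frailty represents residual centre variation, and it removes part of the bias. That stands: having both in one model is neither a contradiction nor an error. A reader might infer from the wording of the plan that it contradicts itself, and the text does not support that.

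A reader might also infer that the technique hazard ratios are in fact confounded by centre. The documents do not show this. They report no link between technique use and centre risk, and at zero correlation the frailty estimate is unbiased. Case mix, implant era and centre volume are already planned adjustments (the last two when available), and only correlation remaining after them matters. The simulations behind the 1.05-1.2 range did not include those covariates. Step 5 shows that volume alone does not remove the bias, but the residual correlation may be below 0.3.

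Thirdly, the within-centre estimate looks clean in Step 3 because no patient-level confounding was simulated. With modest unmeasured confounding of that kind (0.4 SD on both the technique logit and the log-hazard, assumed; true HR 1.00), the results were:

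- correlation 0: frailty 1.11-1.15, with centre proportion 1.17-1.18;
- correlation -0.3: 1.02 against 1.17;
- correlation +0.3: 1.22 against 1.15-1.17.

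Either estimate can be the worse one. This stands too, and it rules out simply replacing the frailty result.

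Finally, scope. The article names an Andersen-Gill model for shocks and a Wei-Lin-Weissfeld model for complications, so the point is confined to the frailty Cox model. A full analysis plan, not shown, may already contain a centre-stratified analysis. The article does, however, name a method and the job it is to do, and a random effect does that job only in part.

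**Conclusion.** The concern holds in conditional form. If a centre's technique use is related to its residual risk after the planned adjustment, the frailty Cox model leaves part of that relation in the technique hazard ratio. If not, there is no bias by this route. Under an assumed centre log-hazard SD of 0.3-0.4 and a correlation of 0.3-0.5, a null technique appears with an HR of about 1.05-1.2. None of these inputs is in the article, and the lower end is small: in a run with SD 0.3 and correlation 0.3, rejection was 8%, close to nominal.

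What the plan lacks is a stated analysis that would tell the two situations apart. Centre volume, the cut at 100, the calendar and device strata and the propensity-score list do not supply it. It is worth correcting because technique contrasts are among the cohort's declared questions and the remedy is cheap.

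**What to change.** Keep the frailty Cox model. For each practice predictor (incision technique, generator position, anesthesia type, defibrillation testing), also report a within-centre estimate beside it, obtained in one of two ways:

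- a Cox model with the baseline hazard stratified by centre; or
- the frailty model with the centre's proportion using that practice added, reading the patient-level coefficient as the within-centre effect. The coefficient of the proportion then shows directly how far the between-centre contrast departs from it.

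State in advance that a technique effect will be interpreted as such only where the frailty and within-centre estimates agree, with the wider within-centre interval in view, and that a difference will be reported as a possible centre effect. Add that agreement does not exclude confounding by indication, which the within-centre estimate leaves in place. That is why it accompanies the frailty estimate and does not supersede it.

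Cost: no new data, and four or five extra terms in a model or one extra model per endpoint. Within-centre intervals are about 10-40% wider, towards the upper end for practices that hardly vary within a centre.
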